## Abstract

**Introduction:**

Hyperglycaemia is common in the very preterm infant and has been associated with adverse outcomes. Preventing hyperglycaemia without increasing the risk of hypoglycaemia has proved challenging. The development of real-time continuous glucose monitors (CGM) to inform treatment decisions provides an opportunity to reduce this risk. This study aims to assess the feasibility of CGM combined with a specifically designed paper guideline to target glucose control in the preterm infant.

**Methods and analyses:**

The Real Time Continuous Glucose Monitoring in Neonatal Intensive Care (REACT) trial is an international multicentre randomised controlled trial. 200 preterm infants ≤1200 g and ≤24 hours of age will be randomly allocated to either real-time CGM or standard care (with blinded CGM data collection). The primary outcome is time in target 2.6–10 mmol/L during the study intervention assessed using CGM. Secondary outcomes include efficacy relating to glucose control, utility including staff acceptability, safety outcomes relating to incidence and prevalence of hypoglycaemia and health economic analyses.

**Ethics and dissemination:**

The REACT trial has been approved by the National Health Service Health Research Authority National Research Ethics Service Committee East of England (Cambridge Central); Medical Ethics Review Committee, VU University Medical Centre, Amsterdam, The Netherlands and the Research Ethics Committee, Sant Joan de Déu Research Foundation, Barcelona, Spain. Recruitment began in July 2016 and will continue until mid-2018. The trial has been adopted by the National Institute of Health Research Clinical Research Network portfolio (ID: 18826) and is registered with anInternational Standard Randomised Control Number (ISRCTN registry ID: 12793535). Dissemination plans include presentations at scientific conferences, scientific publications and efforts at stakeholder engagement.

**Trial registration number:**

ISRCTN12793535; Pre-results.

Strengths and limitations of this studyThe comparison of real-time continuous glucose monitoring (CGM) data with blinded CGM data in the control study arm will provide detailed comparable data on efficacy and safety between study arms.As an international multicentre trial, the results will be generalisable across a range of neonatal intensive care settings.Input by staff and parents within the trial itself as well as part of the trial management will provide information on utility and facilitate translation of the outcomes into clinical practice.The study requires recruitment within 24 hours of preterm birth which requires a significant commitment from the clinical and research teams if it is to be successful.The study is powered to detect a difference in the primary outcome ‘time in target’ (2.6–10 mmol/L), but will not have the power to detect the impact on clinical outcomes.

## Introduction

In utero, glucose levels are normally maintained between 4 and 6 mmol/L,^1^ but infants born preterm are at risk of both hyperglycaemia and hypoglycaemia.^2^ Hyperglycaemia and hypoglycaemia have both been associated with increased mortality and morbidity of preterm babies.^3 4^ Hyperglycaemia can lead to acute problems of a persistent osmotic diuresis and metabolic acidosis which can be difficult to control and has been associated with increased risk of intraventricular haemorrhage and patent ductus arteriosus.^5^ Hyperglycaemia has also been associated with increased long-term morbidity, including increased risk of retinopathy of prematurity.^4 6–8^ Hypoglycaemia is associated with characteristic occipital temporal lesions.^8^ Attempts to reduce risks associated with hyperglycaemia in adult and paediatric and neonatal intensive care (NICU) have resulted in increased risk of hypoglycaemia.^9–11^ This is of particular concern for the very preterm infant in whom there is very varied insulin sensitivity, which increases the risk of hypoglycaemia. In addition the developing brain appears to be particularly vulnerable to both hyperglycaemic^12^ and hypoglycaemic insults. Early postnatal glucose control may be an important modifiable risk factor for clinical outcomes. A recent Cochrane review has highlighted the need for further studies into the impact of interventions to improve glucose control in these infants.^13^

Managing glucose control is dependent in part on methods of measuring and monitoring glucose levels. Within NICU glucose measurements are currently limited to intermittent blood sampling,^14^ with long periods when glucose levels are unknown. In contrast, other physiological parameters such as oxygen saturation, blood pressure and heart rate are all monitored continuously to prevent wide fluctuations. It is increasingly thought that fluctuations in glucose levels may also have a significant impact on long-term outcomes.^15^ The reason for the intermittent measurement is that current methodologies rely on blood sampling either from a central arterial line or by heel prick. Clinical care for preterm infants aims to reduce the frequency of handling^16^ and volume of blood sampled as this has been shown to improve outcomes.

Developments in the measurement of glucose levels in patients with diabetes mellitus include continuous glucose monitoring (CGM) of interstitial glucose levels.^17^ Real-time data on interstitial glucose levels now provides information on glucose trends with the potential for earlier intervention and prevention of both hyperglycaemia and hypoglycaemia. Benefits within adult intensive care remain controversial,^18^ however, the benefits in the setting of NICU may be more marked as blood glucose (BG) measurements are taken much less frequently in these small babies. There have also been key developments in the technology including extended life of sensors (previously 72 hours) and improved accuracy.^19^ The latter is particularly relevant due to the threshold levels of hypoglycaemia and hyperglycaemia (<2.6 and >10 mmol/L) which are more extreme than in adults and are at the limits of accuracy of many methods of glucose measurement.

Blinded CGM has been used in preterm babies within clinical trials,^2 20 21^ and studies of real-time devices have shown a benefit in providing early warning of and prevention of hypoglycaemia.^22^ Studies have not so far attempted to use CGM to guide clinical management to support the targeting of glucose control in preterm infants. A single-centre feasibility study of the real-time monitors demonstrated that sensor glucose (SG) values are comparable with BG values (Real Time Continuous Glucose Monitoring in Neonatal Intensive Care (REACT) feasibility study REC Ref: 14/EE/0127). Data from the feasibility study have helped to design this randomised controlled trial. This multicentre randomised controlled trial will determine whether real-time CGM, with support from a paper algorithm, can help improve the management of glucose control in terms of efficacy, safety and clinical acceptability. This will not only enhance the short-term management of glucose control in infants requiring intensive care but by reducing the risks associated with both hyperglycaemia and hypoglycaemia may impact on long-term clinical outcomes.

## Trial objectives

The REACT trial will evaluate efficacy, safety, utility and cost-effectiveness of real-time CGM in preterm infants in NICU. Our primary hypothesis is that the use of real-time CGM will improve the time a baby’s glucose levels (measured using CGM) remain within the target 2.6–10 mmol/L (widely accepted clinical target for glucose control), compared with standard clinical practice (with blinded CGM data collection). Secondary objectives include evaluation of clinical acceptability in the preterm infant (using staff and parent questionnaires) and safety in relation to the device itself and risk of hypoglycaemia.

## Methods

### Study design

This is a multicentre interventional, randomised controlled trial of CGM compared with standard clinical management (control). We will recruit potential participants within 24 hours of birth and continually monitor their glucose levels for 6 days. Data will be collected until 36 weeks corrected gestational age. No other aspects of concomitant care are prohibited during the trial.

### Eligibility criteria

#### Inclusion criteria

Infants who have a birth weight ≤1200 g, are ≤24 hours of age, ≤33+6 weeks gestation and in whom written informed parental consent has been received.

#### Exclusion criteria

Any lethal congenital abnormality known at trial entry, any congenital metabolic disorder known at trial entry and any neonates who, in the opinion of the treating clinician at trial entry, have no realistic prospect of survival.

### Intervention

Babies will be randomised in a 1:1 ratio, into control and intervention arms of the study using a web randomisation system, Trans European Network ALEA software (TENALEA). This is an open study in which the clinical staff, research team and parents will be aware of the study arm and intervention. All babies will have a subcutaneous sensor inserted, Enlite (Medtronic) that will be linked to a Medtronic MiniMed 640G system and will be calibrated with point of care BG levels. For consistency across sites calibration will be standardised by providing all units with Nova StatStrip meters.

#### Standard care with blinded CGM data collection (control)

These infants will have their glucose control monitored and managed according to standard clinical practice using intermittently sampled BG levels. Nutritional delivery (including glucose) and insulin delivery will be prescribed according to the standard clinical guidelines within each unit. The CGM device will collect glucose data continuously, but the clinical team will be blinded to the data as the monitor will be kept covered and fastened with a tamper proof seal.

#### Real-time CGM device with paper algorithm (intervention)

The CGM data will be open to view by the clinical team during the first week of the baby’s life and the staff will be advised to read and record the SG data hourly as part of standard clinical monitoring. This will support staff to use the additional data available from real-time monitoring to guide timing of BG measurement and changes in clinical management. Interventions to target glucose control will then be guided by the specifically designed paper algorithm (Supplementary file). This algorithm was developed during the REACT feasibility study (REC Ref: 14/EE/0127).

10.1136/bmjopen-2017-020816.supp1Supplementary file 1

### Medical devices: MiniMed 640G system

The MiniMed 640G system is indicated for glucose monitoring and for continuous delivery of insulin, for the management of diabetes mellitus in persons requiring insulin. Monitoring equipment only will be used for this study. The system being used comprises linking the Enlite sensor (Medtronic, Northridge, California, USA) using the Guardian 2 Link transmitter to the MiniMed 640G which then displays the glucose data in real time.

#### Sensor

The Enlite sensor (Medtronic) is a CGM sensor which received CE mark in 2013 (CE certificate No. 21024). The sensor (figure 1) comprises a disposable subcutaneous oxidase-based platinum electrode that catalyses interstitial glucose generating an electrical current every 10 s which is transmitted to a monitor for display and/or recording. The data will be recorded and/or displayed as an averaged value every 5 min, giving a total of 288 readings per day. Glucose values outside the range 2.2–24.0 mmol/L (40–430 mg/dL) are reported as <2.2 mmol/L (40 mg/dL) or >24 mmol/L (430 mg/dL), respectively.

**Figure 1 F1:**
[figure not shown]
The Enlite glucose sensor (Medtronic, Watford UK).

The sensor will be inserted subcutaneously (into the thigh) by hand, not using the standard insertion device, thus ensuring the sensor is inserted into the subcutaneous tissue. The sensors are soft and flexible, approximately 8.75 mm in length and are mounted inside a hollow needle to allow for subcutaneous insertion. Once the sensor is inserted the introducer needle will be withdrawn, and the sensor attached to a small Guardian 2 Link transmitter (CE Mark 2013; Certificate No. 8858) for data transfer to the MiniMed 640G system for data viewing. The sensor will then be secured with a clear occlusive dressing (again trimmed to ensure minimal contact with the infant’s skin), so that the insertion site can be inspected daily. A blood sample will be required in every 12 hours to ensure calibration of the sensor. Sensors will be removed after 7 days.

#### Guardian 2 Link transmitter

It connects to the glucose sensor and sends glucose data wirelessly to the MiniMed640G device (figure 2).

**Figure 2 F2:**
[figure not shown]
The Enlite glucose sensor with The Guardian 2 Link transmitter attached.

#### The MiniMed 640G device

The 640G device as well as providing continuous glucose values will store data so that it can be analysed to track patterns and improve glucose management. Glucose data will be downloaded from the 640G at the end of the study period to a computer for analyses. This device received CE mark in 2014 (CE certificate No. 8857) (figure 3).

**Figure 3 F3:**
[figure not shown]
MiniMed 640G (Medtronic, Watford UK).

## Blinding

To ensure that the real-time data are not available to staff caring for babies in the control arm of the study the CGM will be kept secure in an opaque bag with tamper tag seals. The bags will be opened for calibration in every 12 hours, and each baby will have a log kept of timings of when the tamper tag is broken/resealed.

## Outcomes

The primary outcome is percentage of time SG in target range of 2.6–10 mmol/L. This was selected after consultation as it represents internationally, the clinically most widely accepted target range for glucose control for this population.

Secondary outcomes have been selected to provide further evidence around efficacy, acceptability and safety. These include for efficacy:Mean SG.Percentage of time SG in range of 4–8 mmol/L.SG variability within individuals as assessed by within patient SD.Percentage of time glucose levels in hyperglycaemic range, SG >15 mmol/L.

Acceptability will be assessed by a specifically designed staff questionnaire which will be completed anonymously on day 3 and 7 by the clinical team caring for the baby as well as a parent questionnaire on day 7.

Safety outcomes include both measures of BG and SG to address potential differences in methodologies and to provide data on prevalence of exposures that may be undetected clinically in the control arm of the study:Incidence of hypoglycaemia defined as any episode of BG >2.2 mmol/L and <2.6 mmol/L.Incidence of hypoglycaemia defined as continuous episode of CGM SG <2.6 mmol/L for >1 hour.Incidence of severe hypoglycaemia defined as any episode of BG ≤2.2 mmol/L.

Health economics: cost-effectiveness will be expressed in terms of incremental cost per additional case of adequate glucose control between 2.6 and 10 mmol/L.

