## Sample size

Based on data from the REACT feasibility study and historical control data, we conservatively assume that the SD of the primary endpoint is 22%. A sample size of 200 participants will enable a treatment effect of a 10% increase in the mean value of the primary endpoint to be detected with 90% power using a two-sided 5% significance test in the primary analysis. Based on a consensus of expert opinion a difference of 10% is believed to be of minimal clinical relevance. It is expected that a small number of patients will be withdrawn from the study. Reasons for these withdrawals include transfer to participant’s local NICU, withdrawal of parental consent or death.

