## Data analyses

The primary endpoint will be analysed using linear regression to estimate the absolute difference in time SG in target of 2.6–10 mmol/L, adjusting for baseline variables (centre, gestation). Analyses will be undertaken both for intention to treat and as treated populations. Estimates of treatment effect, with 95% CIs and p values will be provided. Secondary endpoints that are continuous variables will be analysed in a similar fashion. Secondary endpoints that are counts or binary variables will be analysed using an appropriate regression framework. Methods will be used to reduce the likelihood of a type I error. All of the efficacy endpoints will be ranked in order of importance: mean SG, percentage of time SG in target of 4–8 mmol/L, SG variability within individuals as assessed by within-patient SD, percentage of time glucose levels in hyperglycaemic range—SG >15 mmol/L.

Continuous variables will report the mean, median, SD, range, maximum and minimum. Binary or categorical endpoints will be represented using frequency tables in the ‘p% (r/n)’ format. The analysis will look for a treatment interaction effect with the following baseline variables: centre, sex, corrected gestational age, birthweight SDs, use of antenatal steroids, maternal chorioamnionitis and maternal diabetes using the regression framework in an exploratory, non-confirmatory manner.

An incremental cost-effectiveness analysis will be performed. In the baseline analysis, the economic evaluation will be expressed as the incremental cost per additional case of adequate glucose control. Adequate control will be considered as 80% of time in target. Given the multinational nature of the trial, the hierarchical structures of the cost and outcomes data will be taken into account in the analysis plan. Due to the known limitations of within-trial economic evaluations, we will also construct a decision-analytical model to model the cost-effectiveness of CGM beyond the time horizon of the trial.

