### During the intervention period of the study (study days 1–7)

The following expected SAEs will need to be recorded in the CRF (safety log) and reported using the safety report form to the sponsor within 24 hours of awareness of the event: (1) death, (2) culture positive infection, (3) severe hypoglycaemia (<2.6 mmol/L), (4) seizures, (5) any other related SAE.

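### The blood glucose outcome labelled hypoglycaemia covers only the band 2.2–2.6 mmol/L, no outcome counts every infant with blood glucose below 2.6, and the band alone does not track harm

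*Protocol article*

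**What the plan says.** The Outcomes section of the protocol article lists three hypoglycaemia outcomes under safety:

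- "Incidence of hypoglycaemia defined as any episode of BG >2.2 mmol/L and <2.6 mmol/L"
- "Incidence of hypoglycaemia defined as continuous episode of CGM SG <2.6 mmol/L for >1 hour"
- "Incidence of severe hypoglycaemia defined as any episode of BG ≤2.2 mmol/L"

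The Introduction describes the clinical limits as "threshold levels of hypoglycaemia and hyperglycaemia (<2.6 and >10 mmol/L"), with no floor on the hypoglycaemic side.

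The safety outcomes are among the secondary outcomes. On these the Data analyses section says: "Secondary endpoints that are counts or binary variables will be analysed using an appropriate regression framework". The ranking by importance in that section covers efficacy endpoints only.

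The description of the intervention arm says that staff are meant to use the real-time sensor data in deciding when to measure BG. Control infants are sampled intermittently under local practice.

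**The concern.** The first BG outcome carries the plain label hypoglycaemia but is closed at both ends. An infant whose only low BG is 2.0 mmol/L does not have hypoglycaemia by this rule. An infant at 2.4 does. The SG outcome and the Introduction use below 2.6 with no lower limit, so the same word covers different sets of infants.

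Two things follow. First, the ordinary safety quantity, the number of infants with any BG below 2.6, is not a listed outcome. Second, a regression comparing the arms on the band treats a move out of it as an improvement, whether the infant moved up to normal values or down to severe ones. Hypoglycaemia is the main safety question for this intervention, so its BG measure should move in one direction as harm increases.

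**Working it through.** **Plan's own figures.** The article gives no hypoglycaemia rate, so there is no figure on this point to reproduce. The sample size concerns the primary endpoint and is used here only to set 100 infants per arm. With SD 22, difference 10, 90% power and two-sided 5%: n per arm = 2 × (1.960 + 1.282)² × 22² / 10² ≈ 101.7, rounded up to 102, or 204 in total against the stated 200. Power at 100 per arm is 89.5%. The stated figure reproduces and is unaffected by this point.

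**Step 1: how individual infants are classified (from the definitions alone).**

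| Low BG readings (mmol/L) | Band outcome | Severe outcome | Any BG <2.6 |
|---|---|---|---|
| 2.4 only | yes | no | yes |
| 2.0 only | no | yes | yes |
| 2.4 and 2.0 | yes | yes | yes |

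The second infant is worse off than the first but does not count in the band. The third counts in both rows, because each definition asks for any episode.

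The first two rows also show the effect of sampling time. Take one falling glucose. If the sensor prompts a sample at 2.4 and nothing lower is measured, the band counts it. If the first sample is at 2.0, the band does not. Catching falls earlier can therefore raise the band outcome.

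**Step 2: whether the two BG rows give the total.** Let B be infants in the band row, S infants in the severe row and O infants in both. Then any BG <2.6 = B + S − O, with O anywhere from 0 to the smaller of B and S. The listed outcomes do not give O. With assumed rows B = 20, S = 5 in one arm and B = 10, S = 15 in the other:

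- first arm: between 20 and 25 infants
- second arm: between 15 and 25 infants
- second minus first: between 15 − 25 = −10 and 25 − 20 = +5

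The two rows alone do not fix even the sign of the difference in any BG <2.6.

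**Step 3: a shift from mild to severe (assumed counts, 100 per arm).** In control, 20 infants have their lowest BG in the band and 5 have BG ≤2.2 with no band reading. In intervention, 10 of the 20 move to ≤2.2, and a fraction q of those 10 also have a reading in the band.

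- Band row: 20 − 10 × (1 − q)
- Severe row: 5 + 10 = 15
- Any BG <2.6: 25 in both arms

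| q | Band row, control → intervention | Change in band | Severe row | Any BG <2.6 |
|---|---|---|---|---|
| 0 | 20 → 10 | −10 | 5 → 15 | 25 → 25 |
| 0.25 | 20 → 12.5 | −7.5 | 5 → 15 | 25 → 25 |
| 0.5 | 20 → 15 | −5 | 5 → 15 | 25 → 25 |
| 0.75 | 20 → 17.5 | −2.5 | 5 → 15 | 25 → 25 |
| 1 | 20 → 20 | 0 | 5 → 15 | 25 → 25 |

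With a shift of 5 infants and q = 0, the changes are −5, +5 and 0, whether the assumed control counts are 20 and 5, 15 and 3, or 10 and 2. In the most extreme row of the table (q = 0), Fisher's exact test gives p = 0.073 for the band and p = 0.032 for the severe outcome.

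**The case against.** The strongest reply is that the two BG outcomes are adjacent grades which together cover every BG below 2.6 mmol/L. A reader might infer from the band definition that the worst values go uncounted, or that deepening hypoglycaemia would be reported as a safety gain. The article does not support either inference. The infant at 2.0 is counted under the more serious label. In every row of the illustration the severe outcome rises by 10, and at q = 0 it gives the clearer statistical signal. The SG outcome has no floor and would pick up sustained deep episodes. Only someone who reads the band row alone would be misled. This part of the objection stands.

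It is also fair that the counts are assumed, that the apparent fall vanishes when every shifted infant has a band reading, and that these outcomes lie outside the ranked efficacy endpoints. Sampling that differs by arm affects any BG outcome, including a cumulative one, because more sampling finds more low values. That BG and SG differ is partly by design, since the article includes both to allow for differences between the methods.

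Two things survive. Reading both rows together shows a shift but still does not give the number of infants below 2.6, because the overlap is unknown. And the SG outcome cannot stand in for that number, since it requires more than an hour below the threshold and comes from another measurement.

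**Conclusion.** The point holds in a limited form. The band outcome cannot be read by itself as incidence of hypoglycaemia. It is not monotone in harm, it departs from the article's own threshold of below 2.6 mmol/L, and together with the severe row it does not yield the total below that threshold. These statements follow from the definitions and need no assumed rates.

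The size of any distortion is unknown. On the assumed counts the band row changes by between −10 and 0 per 100 infants for a shift of 10. The larger value requires that no shifted infant has a reading in the band. The documents do not support saying that a mild-to-severe shift would look like a benefit in the trial's results, because the severe outcome is listed alongside and would rise. This is a defect of definition and labelling in a secondary safety outcome. It is inexpensive to correct and does not touch the primary analysis.

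A separate inconsistency lies nearby: the reporting rules for study days 1–7 refer to "severe hypoglycaemia (<2.6 mmol/L"), whereas the outcome list sets severe at 2.2 or below. Those sections must be reconciled. Nothing here depends on which is kept.

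**What to change.** For the between-arm analysis, define the BG outcome per infant as any BG below 2.6 mmol/L, with any BG of 2.2 mmol/L or less as a nested outcome. Keep the 2.2–2.6 band as a descriptive row only, labelled as the milder range and printed beside the severe row.

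This makes the BG outcome consistent with the Introduction and the SG threshold, and an infant counts whether first sampled at 2.4 or at 2.0. It does not remove differences in detection due to how often each arm is sampled, so the result should be read with the SG outcome, which is collected continuously in both arms.

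The cost is one line of outcome wording, to be settled before the arms are compared. The BG values are already collected, and the sample size does not change.

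### Severe hypoglycaemia is counted only from blood samples whose timing the sensor can guide in one arm, so its between-arm comparison is open to differential ascertainment; a sensor-based severe outcome should be added

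*Protocol article*

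**What the plan says.** The Outcomes section of the protocol article lists three hypoglycaemia outcomes.

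- BG above 2.2 and below 2.6 mmol/L, any episode.
- SG below 2.6 mmol/L continuously for more than 1 hour.
- The severe outcome: "Incidence of severe hypoglycaemia defined as any episode of BG ≤2.2 mmol/L".

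The same section explains that BG and SG measures are paired partly "to provide data on prevalence of exposures that may be undetected clinically in the control arm of the study".

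BG is obtained differently in the two arms. In the intervention arm staff are advised to read and record SG hourly and to "use the additional data available from real-time monitoring to guide timing of BG measurement". Control infants are "monitored and managed according to standard clinical practice using intermittently sampled BG levels", and there "the clinical team will be blinded to the data as the monitor will be kept covered and fastened with a tamper proof seal".

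Two features are common to both arms. Under the sensor description, "A blood sample will be required in every 12 hours to ensure calibration of the sensor". The sensor stores an averaged value every 5 minutes, and "Glucose values outside the range 2.2–24.0 mmol/L" are recorded only as lying below or above that range.

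**The concern.** A BG-defined event needs both a low glucose and a blood sample taken while it is low. In the intervention arm a falling SG trace can prompt that sample. In the control arm it cannot, except when the bag happens to be open for calibration. The outcome therefore mixes the true risk of severe hypoglycaemia with the chance of being sampled, and the second part depends on allocation.

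Adjusting the regression for centre and gestation, the only covariates the Data analyses section names for its adjusted model, does not remove this. The difference arises from the allocated treatment and not from a baseline imbalance.

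The article opens by describing the challenge of preventing hyperglycaemia without more hypoglycaemia, and it names hypoglycaemia risk as a safety objective. An outcome that tends to over-record severe events under real-time monitoring could suggest harm where there is none, or hide a real reduction. If visible SG instead led staff to take fewer blood samples, the outcome could hide harm.

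**Working it through.** **What the document gives.** There is no event rate for severe hypoglycaemia, no routine BG interval in either arm, and no sample-size figure for this outcome. The only figure that can be reproduced is for the primary endpoint: n per arm = 2 × (1.960 + 1.282)² × 22² / 10² = 101.7, so 102 per arm or 204 in total, against the stated 200. With 100 per arm, power is 89.5%. That figure is sound and is not affected. It is used below only for the arm size of 100.

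**Ascertainment by outcome.**

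| Outcome | Source | Equal ascertainment by design? | Separates severe? |
|---|---|---|---|
| BG >2.2 and <2.6 | blood | no | no |
| SG <2.6 for >1 hour | sensor | yes, given equal wear and calibration | no |
| BG ≤2.2 | blood | no | yes |

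The only outcome that isolates severe episodes is one without equal ascertainment.

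**Formula.** Observed risk = true risk × probability of detection. Hence observed RR = true RR × (detection in intervention / detection in control).

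**Assumed detection (not in the document).** Four pairs, written control / intervention:

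| Pair | Ratio | True RR 1.0 appears as | True RR 0.5 appears as |
|---|---|---|---|
| 0.70 / 0.90 | 0.90/0.70 | 1.29 | 0.64 |
| 0.30 / 0.50 | 0.50/0.30 | 1.67 | 0.83 |
| 0.50 / 0.90 | 0.90/0.50 | 1.80 | 0.90 |
| 0.30 / 0.80 | 0.80/0.30 | 2.67 | 1.33 |

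These are chosen pairs, not bounds. Crossing the extremes of the same ranges would give 0.90/0.30 = 3.0 at one end and 0.50/0.70 = 0.71 at the other. The second value is the reversed case.

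**Chance of a false signal.** Take 100 infants per arm, equal true risk, and a two-sided 5% pooled test of two proportions, with all outcomes enumerated exactly. Over the four pairs, the chance of a nominally significant excess in the intervention arm is:

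- 5% to 17% if 5% of infants truly have an episode;
- 8% to 33% if 10% do;
- 12% to 64% if 20% do.

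The nominal rate in that direction is 2.5%. The true risks of 5%, 10% and 20% are also assumed.

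**How much the calibration samples help.** Under sampling unrelated to glucose, an episode of length L is caught by samples I hours apart with probability L/I. A 1-hour episode is caught with probability 1/12 = 8% by the 12-hourly calibration samples alone. It is caught with probability 1/4 = 25% by 4-hourly sampling, an assumed interval. The shared samples therefore guarantee only a low common floor of detection for short episodes.

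**What a sensor outcome would do.** The sensor samples both arms every 5 minutes. With the same definition in each arm, and equal wear and calibration, the detection ratio is 1 and the observed RR equals the true RR for sensor-defined events.

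**The case against.** The authors saw the general problem. They pair BG with SG because control-arm exposures may go unnoticed, and the Safety section says hypoglycaemia is assessed from both. The SG outcome has no lower bound, so an SG of 2.2 or less lasting over an hour already counts in it. This stands: a reader might infer that severe hypoglycaemia has no sensor measure at all, and that would be wrong. What is missing is a separate severe category and any cover for episodes of an hour or less.

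A reader might also infer a very large bias. If every episode lasts 1 hour, controls are sampled only every 6 to 12 hours and without regard to symptoms, and the intervention arm catches nearly everything, the spurious risk ratio is 6 to 12. The document does not support this. Twelve hours is the calibration interval and not the clinical one, the routine interval is not given, clinically prompted control tests are ignored, and hourly reading is only advised. The text says SG guides BG timing, not that it dictates it. Nor is the direction certain.

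It would also be too strong to call this the trial's only severe safety comparison. Mortality, morbidity and device effects are assessed as well.

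Finally, part of the remedy could sit in an analysis plan that is not shown. That applies to caveats and to BG test counts. It does not apply to the outcome definition, which this article fixes.

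**Conclusion.** The point holds in a limited form. As defined, the BG ≤2.2 mmol/L comparison is subject to differential ascertainment, and the existing SG outcome does not replace it at the severe level. The likely direction is over-detection in the intervention arm, with the reverse possible. The size cannot be derived from the document. The apparent risk ratio of about 1.3 to 2.7 under no true difference rests entirely on the four assumed detection pairs, and it shows only that moderate differences in detection are enough to matter.

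This is something the sponsor should fix, but it is not critical to the trial. It concerns one secondary safety outcome, and the primary outcome, time with SG in the 2.6–10 mmol/L range, is measured by the same sensor in both arms.

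**What to change.** 1. Add a severe hypoglycaemia outcome from SG at the sensor's lower reporting limit, worded identically for both arms: the percentage of time there, and the incidence of episodes with a prespecified minimum duration. A single 5-minute value should not define an episode. To cover what the present SG outcome misses, the duration needs to be shorter than its 1 hour.
2. Make this the main between-arm comparison for severe hypoglycaemia.
3. Keep the BG ≤2.2 mmol/L outcome. Report it with the number of BG tests per infant-day by arm, where these are recorded, and state that its between-arm comparison is subject to differential ascertainment. Restricting BG to the calibration samples is not a good substitute, given the 8% capture of a 1-hour episode shown above.
4. Separately, the safety reporting list describes severe hypoglycaemia as below 2.6 mmol/L, while Outcomes uses 2.2 or less. The two passages must be reconciled so that the term has one meaning.

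The cost is wording and analysis only. The SG data are already recorded in both arms, and neither the sample size nor clinical management changes. The downside is weaker sensor accuracy near its floor. The Introduction itself notes that the 2.6 and 10 mmol/L thresholds are at the limits of many methods, and 2.2 is lower still. Values below 2.2 are only flagged, so depth cannot be measured. The BG result should therefore be shown beside the SG result.
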